### Provisions for post-trial care {30}

A general practitioner and a nurse will be present at each visit to monitor the participants’ well-being during and at the end of the session. Following blood sampling, the participants will be assessed for any potential adverse incidents. Signs and symptoms, such as dizziness, puncture site bleeding, shortness of breath, blood pressure, and imbalance, will be carefully evaluated for any necessary intervention.

### Outcomes {12}

The primary outcome of this trial is to determine the effect of a 10-h TRE compared to standard dietary recommendations on indices of arterial stiffness among men with MetS. The secondary outcomes consist of changes in anthropometric parameters, indirect calorimetry parameters, lipid profile (triglyceride, total cholesterol, LDL, and HDL), liver enzyme tests (AST, ALT, and ALP), FBG and insulin concentrations, insulin resistance (assessed by HOMA-IR) [19], appetite status, cognitive outcomes (assessed by GNG test and WCST), quality of life assessment (WHOQOL-BREF questionnaire), sleep quality (PSQI questionnaire), physical activity assessments (IPAQ and pedometer), and 3-day food and drink diary.

### Participant timeline {13}

The schedule of enrolment, interventions, and assessments is shown in Table 1.

### Sample size {14}

The sample size was calculated according to the percentage of PWV change in the study by Sutton et al. [13]. Considering an alpha error of 5%, beta error of 20%, and an effect size of 0.63, a sample size of 20 was estimated for each of the two study groups.$$n=\frac{{{\left({z}_{1-^{\alpha }\!\left/ \!_{2}\right.}+{z}_{1-\beta }\right)}^{2}(\sigma }_{1}^{2}+{\sigma }_{2}^{2})}{{\left({\mu }_{1}-{\mu }_{2}\right)}^{2}}$$$$n=\frac{{\left({Z}_{1-^{\alpha }\!\left/ \!_{2}\right.}+{Z}_{1-\beta }\right)}^{2}}{{f}^{2}}$$

Taking into account a 20% loss to follow-up, 24 participants will be enrolled in each group.

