**Methods:**

Forty-eight participants will be assigned to either TRE or control groups using simple randomization. The TRE group will consume their meals during a 10-h period and experience 14 h of fasting. They will also be advised to consume their last meal no later than 20:00. Both groups will receive standard dietary advice. The participants will be followed for 6 weeks. The primary outcome will be changes in PWV. Laboratory measurements, including lipid profile, liver enzyme tests, fasting blood glucose (FBG), insulin concentrations, and insulin resistance, as well as anthropometric data, blood pressure, basal metabolic rate, appetite status, physical activity level, sleep quality, cognitive function, quality of life, and calorie intake, will be evaluated throughout the study.

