## Trial design {8}

This study is designed as a randomized controlled trial (RCT), with parallel groups and an allocation ratio of 1:1, in a superiority design framework. Regarding the allocation of each participant to the control and intervention groups, randomization will be run using computerized random number generation and sealed envelopes will be used to conceal the random allocation. The potential participants will be identified among the population of the PERSIAN Cohort Study in Mashhad University of Medical Sciences and will be recruited through phone calls. Screening, including both physical and laboratory examinations, will be carried out to assess the presence of MetS based on IDF criteria [16]. The study design and planned assessments for each stage of the study are explained in detail, in the following sections, and briefly summarized in Table 1. The study protocol adheres to the checklist of the Standard Protocol Items: Recommendations for Interventional Trials (SPIRIT) guidance (Table 1).

**Table 1 Tab1:** The timeline for the enrollment, intervention, and assessment schedule

	**Timepoint**	**Timeline**				
		**Enrollment**	**Allocation**	**Study period**		
				**Day 1**	**Week 3**	**Week 6**
	**Enrollment**	✔				
	**Eligibility screening**	✔				
	**Informed consent**		✔			
	**Allocation**		✔			

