## Discussion

TRE and intermittent fasting (IF) are being investigated as approaches to improve cardiometabolic abnormalities in both animal and human trials [39–41] and have shown to be effective in various aspects of MetS [11, 15]. We planned a protocol to assess the effect of 10-h TRE on vascular stiffness in men with metabolic syndrome, aiming to contribute to the limited knowledge in this context.

We expect that TRE can efficiently improve arterial stiffness parameters, compared to the control group. The gold standard method of measurement for arterial stiffness is PWV, despite its dependence on age, blood pressure, and heart rate [42]. It can be proposed that the higher the PWV level, the higher the arterial stiffness [43]. The findings from this RCT will provide valuable insights into the potential benefits of TRE on arterial stiffness, which could inform future dietary guidelines and interventions for MetS patients. This study has several strengths including the presence of a control group, assessment of sleep quality as a confounding factor that may affect PWV [44], and assessment of different laboratory and clinical findings. By restricting the study to men and excluding those with a BMI ≥ 35 and comorbid conditions, the study population becomes more homogeneous, which may yield more reliable findings due to reduced confounding factors. The study may be limited in that participants’ diets may differ in terms of food quality. However, collecting detailed food and drink diaries at specific time points throughout the study will allow for assessing food composition. Also, participant recruitment and retention are significant practical issues in conducting this study, primarily due to the difficulties participants face in adhering to the TRE protocol. In this respect, the participants will be regularly followed up to assess study adherence, and a 20% rate of dropout was included in the sample size calculation to allow for attrition rate. Using an intention-to-treat analysis protocol also minimizes the effect of participant dropout.

In conclusion, this study is expected to lead to innovative findings regarding the effects of TRE on arterial compliance. Results from this and other studies can potentially lead to novel therapeutic approaches and help inform dietary guidelines on the timing of eating to improve MetS and cardiovascular outcomes with important individual and public health implications.

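### Enrolling 24 per group allows for a 16.7% loss, not the stated 20% (which would need 25), and simple randomisation of 48 does not in itself give 24 in each group; the effect on power is small

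*Protocol article*

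**What the plan says.** All references are to the protocol article.

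- **Sample size {14}** sets the design values, "Considering an alpha error of 5%, beta error of 20%, and an effect size of 0.63", and reports that "a sample size of 20 was estimated for each of the two study groups". It then inflates for attrition: "Taking into account a 20% loss to follow-up, 24 participants will be enrolled in each group".
- **Discussion** names recruitment and retention as significant practical issues and relies on the allowance in reply: "a 20% rate of dropout was included in the sample size calculation to allow for attrition rate".
- **Abstract, Methods** gives the total and the method of assignment: "Forty-eight participants will be assigned to either TRE or control groups using simple randomization".
- **Trial design {8}** specifies "parallel groups and an allocation ratio of 1:1".
- **Sequence generation {16a}** and **Concealment mechanism {16b}** describe a computer-generated random sequence and sealed envelopes. Neither mentions blocking or fixed arm totals.

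**The concern.** There are two separate issues.

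**Inflation for loss.** The number enrolled appears to have been obtained by adding 20% to the completer target. The percentage lost is a percentage of those enrolled, so the target should be divided by 0.8. If so, the stated allowance does not cover the stated loss. The design has no slack to absorb this, because the printed formula gives 19.78 and 20 is simply the next whole number.

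**Arm sizes.** Unrestricted (simple) randomisation of 48 men leaves the arm sizes to chance, yet the sample size section treats 24 per group as fixed. The two statements cannot both be literally true unless the list was restricted in a way the article does not describe.

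At stake are the accuracy of a published sample-size figure that the Discussion cites as its protection against dropout, and a small amount of power for the primary comparison of pulse wave velocity.

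**Working it through.** **Inputs** (from Sample size {14} unless noted): two-sided alpha 0.05, power 0.80, effect size f = 0.63, target 20 per group, loss 20%, enrolment 24 per group. The total of 48 and simple randomisation come from the Abstract, and the t-test from Statistical methods {20a}.

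**1. Reproduce the base figure.** The second printed formula is n = (z₀.₉₇₅ + z₀.₈₀)² / f².

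(1.960 + 0.842)² / 0.63² = 7.849 / 0.3969 = 19.78, which rounds up to 20. The stated 20 reproduces. Comparing the two printed formulas, f is the mean difference divided by √(σ₁² + σ₂²). With equal SDs this is a standardised difference of 0.63 × √2 = 0.891.

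**2. Inflation for loss.**

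- Stated: 24 = 20 × 1.2.
- Expected completers from 24 at 20% loss: 24 × 0.8 = 19.2.
- Enrolment needed for 20 completers at 20% loss: 20 / 0.8 = 25 per group, 50 in total.
- Loss that 24 does cover: 1 − 20/24 = 16.7%.

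**3. Effect on power.** With equal arms the normal-approximation power is Φ(0.63 × √n − 1.960).

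- n = 20: 0.63 × 4.472 = 2.817, and Φ(0.857) = 80.4%.
- n = 19.2: 0.63 × 4.382 = 2.761, and Φ(0.801) = 78.8%.

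The noncentral t calculation for the planned t-test gives lower values and a similar difference.

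| Completers per group | Normal formula | t-test |
|---|---|---|
| 20 | 80.4% | 78.4% |
| 19.2 | 78.8% | 76.6% |
| Loss of power | 1.6 points | 1.8 points |

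**4. Arm sizes under simple randomisation.** The number in one arm is Binomial(48, 0.5).

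- P(exactly 24:24) = C(48, 24) / 2⁴⁸ = 11.5%
- P(22:26 or more uneven) = 66.5%
- P(20:28 or more uneven) = 31.2%

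**5. What that imbalance costs.** Power after 20% loss in each arm:

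| Allocation of 48 | Normal formula | t-test |
|---|---|---|
| 24:24 | 78.8% | 76.6% |
| 20:28 (16.0 and 22.4 completers) | 77.7% | 75.5% |
| Averaged over simple randomisation | 78.0% | 75.7% |

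Chance imbalance costs on average just under one further point.

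**6. Probability that both arms keep at least 20 men,** with independent 20% loss: 9.6% with simple randomisation of 48, 21.1% with 24:24 fixed, and 38.0% with 25:25 fixed.

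**The case against.** The strongest reply is that this hardly matters: one man per arm, under two power points, and a dropout rate that is itself a guess. That is right about the size, and it makes this a minor point. It does not make the figure correct. The article states a 20% allowance twice and leans on it in the Discussion, and the number beside it does not provide it.

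It could also be said that the intention-to-treat analysis with imputation keeps every man in the analysis. Imputation does not restore the information in pulse wave velocity values that were never observed, and the protocol's own inflation treats completers as the target. This reply does not remove the point.

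On randomisation the reply is stronger. Simple randomisation is valid and unbiased, and a 1:1 ratio describes the allocation probability, which chance imbalance does not contradict. The word simple appears only in the Abstract, and a shuffled list of 24 plus 24 would fit everything in the body of the article. What remains is a mismatch of wording.

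A reader might go further in four ways, none of which the document supports.

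- **That 20 completers per arm will not be reached.** The shortfall is 0.8 of a man per arm in expectation, if loss is exactly 20%. The low probabilities in step 6 look alarming alone, but even a fixed 25 per arm reaches 20 in both arms only 38.0% of the time. An average allowance never guaranteed it.
- **That power falls from 80% to 76%.** This compares a normal-formula figure with a t-test figure. Like for like, the fall is 1.6 to 1.8 points.
- **That power is really about 47%.** That comes from reading 0.63 as an ordinary standardised difference, under which even 20 per arm gives only 49%. It is a separate question about scaling, not a result of the dropout arithmetic.
- **That the trial must switch to permuted blocks.** In an unblinded trial already recruiting, that trades some predictability of allocation for about one power point. It is a design preference, not a correction.

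**Conclusion.** The stated allowance is wrong: 24 per group covers a 16.7% loss, and a 20% loss would need 25. The expected shortfall is 0.8 of a completer per arm, and the cost is 1.6 points of power by the protocol's formula or 1.8 by the planned t-test. This is a minor error that should be corrected because a published design figure does not do what the text says it does.

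The description of randomisation needs reconciling. Taken literally, simple randomisation of 48 and exactly 24 per group agree in about one trial in nine. The average cost of the imbalance is just under one power point, so neither the validity of the comparison nor the 1:1 ratio is in question.

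The power figures assume that 0.63 is scaled as the printed formula scales it, that the SDs are equal, that loss is 20% in each arm, and that lost men contribute no information on the primary outcome. The value 19.2 is an expectation entered as a non-integer sample size.

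**What to change.** 1. In Sample size {14} and in the Discussion, restate the allowance that 24 per group provides as 16.7%. Alternatively, keep 20% and say that it leaves about 19 completers per group, with power of about 77% by the t-test (79% by the protocol's formula). Either is a change of text only and leaves conduct untouched.

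2. If the team prefers the enrolment to match a 20% loss, the figure is 25 per group, 50 in total. That costs two more men. It also needs the ethics approval, participant information and registry notification that the article requires for changes affecting conduct, since recruitment began in October 2023.

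3. Reconcile the Abstract with Sample size {14}. If the list was restricted to equal arms, say so and remove the word simple. If it was not, give 48 as the total and say that the arms are equal only in expectation. This costs one sentence. The allocation scheme need not change mid-trial.

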### Recruitment {15}

The potential participants will be identified from the PERSIAN Cohort Study population at Mashhad University of Medical Sciences based on IDF criteria for MetS. They will be contacted via phone calls and invited to participate.

## Assignment of interventions: allocation

### Sequence generation {16a}

The recruited individuals will be allocated using a computer-generated sequence of random numbers, to the intervention and the control groups.

### Concealment mechanism {16b}

Each participant will receive a sealed envelope containing a random number which will assign them to either the intervention or control group.

### Implementation {16c}

An individual who is not part of the research team will be responsible for creating the allocation sequence, enrolling participants, and assigning them to the interventions.

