#### Exclusion criteria

Individuals who fall under the following categories will be excluded from the study: shift workers, individuals consuming food for less than 14 h per day, those with a documented diagnosis of diabetes mellitus, restrictive diets (e.g., cancer patients), thyroid disorders, eating disorders, receiving dietary supplements other than vitamins or minerals, and those unable to adhere to the TRE protocol.

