### Who will take informed consent? {26a}

The principal researcher will inform eligible individuals about the study details, providing both written and verbal information in clear and comprehensible language. Subsequently, the interested individuals will be asked to provide written consent, in accordance with the standard procedures of the trial. Those who decline to give written consent or demonstrate significant distress will not be included in the study. In the case of illiterate individuals, since our study includes tests requiring literacy, it is not possible to recruit them.

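### One person creates the random sequence, enrols participants and assigns them, so the sealed envelopes do not secure concealment from the enroller

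*Protocol article*

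**What the plan says.** All of the text is in the protocol article.

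- **Implementation {16c}:** "An individual who is not part of the research team" is given three tasks. This person "will be responsible for creating the allocation sequence, enrolling participants, and assigning them to the interventions".
- **Trial design {8}:** "sealed envelopes will be used to conceal the random allocation".
- **Concealment mechanism {16b}:** "Each participant will receive a sealed envelope containing a random number which will assign them to either the intervention or control group".
- **Sequence generation {16a}:** men are "allocated using a computer-generated sequence of random numbers, to the intervention and the control groups". The abstract adds that the randomization is simple: "Forty-eight participants will be assigned to either TRE or control groups using simple randomization".
- **Who will take informed consent? {26a}:** "The principal researcher will inform eligible individuals about the study details", and then seeks written consent.
- **Exclusion criteria:** the list includes "those unable to adhere to the TRE protocol", which calls for a judgement about the individual man.
- **Who will be blinded {17a}:** participants and field researchers are not blinded; the statistician is.

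**The concern.** Allocation is concealed when whoever admits a participant cannot know what the next assignment will be. The usual safeguard is to keep the person who holds the list apart from the person who enrols. This protocol states the opposite arrangement: the same individual does both and also assigns. A sealed envelope hides its content only from people who do not already know the sequence.

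At stake is selective entry. If the next assignment is known, a man's entry can be brought forward, delayed or refused in light of it. Men expected to do well could then be over-represented in one arm, and the difference would read as an effect of time-restricted eating. Analysis by intention to treat and a blinded statistician do not remove this, because the imbalance arises before the data exist. With participants and field staff unblinded, concealment at entry is one of the few protections this design can have.

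**Working it through.** The defect lies in the assignment of roles, so the main check is to compare the sections. The arithmetic only puts a scale on a hypothetical.

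**1. Can the enroller know the next assignment?**

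- Implementation {16c} has the same person create the sequence and enrol.
- Trial design {8} and Concealment mechanism {16b} rely on sealed envelopes. Neither says that someone without the list enrols.
- No other section separates the list-holder from the enroller. As written, the answer is yes.
- Simple randomization prevents anyone from inferring the next assignment from earlier ones. It gives no protection against a person who made the list.

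**2. Is entry fixed before the assignment is revealed?**

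- Table 1 places eligibility screening in the Enrollment column, but ticks informed consent and allocation together in the Allocation column.
- The article does not say that entry is recorded before the envelope is opened.

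**3. Who makes the entry decision?**

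- The consent section has the principal researcher inform men who are already eligible and seek their consent. Implementation {16c} has an outsider enrol.
- Informing and consenting are not the same act as enrolling, so the two sections are in tension rather than in flat contradiction. The article does not say who applies the criterion on ability to adhere.

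**4. What does the planned effect of 0.63 mean in SD units?**

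Sample size {14} gives two formulas:

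- n = (z₁₋α/₂ + z₁₋β)² (σ₁² + σ₂²) / (μ₁ − μ₂)²
- n = (z₁₋α/₂ + z₁₋β)² / f²

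The plan's own figure comes first. With a two-sided alpha of 5% and a beta of 20%, (z₁₋α/₂ + z₁₋β)² = 7.849, and 7.849 / 0.63² = 19.78, which rounds up to the stated 20 per group.

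Equating the formulas gives f² = (μ₁ − μ₂)² / (σ₁² + σ₂²). With equal SDs, f = d/√2, so d = 0.63 × √2 = 0.89 SD. As a cross-check, 2 × 7.849 / 0.89² is about 20 per group. If 0.63 were itself the difference in SD units, the requirement would be 2 × 7.849 / 0.63² = 39.6, or 40 per group, which is not what the protocol states.

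**5. Hypothetical shift from selective entry**

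Assumptions that are not in the documents: k places in one arm go to men whose outcome would be 1 SD better. The arm size of 24 comes from Sample size {14}; simple randomization does not guarantee exactly 24. The shift in the arm mean is k × 1 SD / 24.

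| k | Shift (SD) | Share of 0.89 SD |
|---|---|---|
| 2 | 2/24 = 0.083 | 9% |
| 3 | 3/24 = 0.125 | 14% |
| 5 | 5/24 = 0.208 | 23% |

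**The case against.** The strongest defence has four parts.

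- **Independence.** The individual is outside the research team and so has less reason to steer entry. This stands as a point about motive. It does not remove knowledge of the list.
- **Unpredictability.** The sequence is computer-generated and simple, and the envelopes can still hide it from the unblinded field researchers. This also stands for anyone without the list. It does not cover the person who made the list and enrols.
- **A benign reading of the roles.** Table 1 puts screening before allocation, and the consent section speaks of men who are already eligible. The team may screen and consent while the outsider only registers and assigns, so that those who judge eligibility never see the list. This is a fair possibility and it limits what can be claimed. But Implementation {16c} gives the outsider enrolment in terms, and on the benign reading that section is worded wrongly and still needs amending.
- **The remedy has its own weakness.** Data management {19} has the primary investigator collect all data, so moving entry decisions to the principal researcher may give them to someone who knows past assignments. Under simple randomization, past assignments do not reveal the next one. What matters is that whoever enrols has no access to the list.

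A reader might infer more than the text supports. It does not show that allocation has been or will be subverted, nor that the outsider applies the criterion on ability to adhere, because no section says who does. The consent and implementation sections do not flatly contradict each other. Nor should 0.125 SD be compared directly with 0.63 to give a fifth, since the protocol's 0.63 is not in SD units. It would also be too much to call selective entry the only bias that intention to treat and baseline adjustment leave unrepaired; outcome-dependent dropout and unblinded outcome measurement are others.

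**Conclusion.** The point holds as a risk created by a stated arrangement. The enroller, as described, can know the next assignment, and the sealed envelopes do not secure concealment from that person. It is not a matter of detail left to a fuller document, because the article positively assigns the three tasks to one individual.

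The size of any resulting bias cannot be estimated from the documents. The illustrative shift of 0.125 SD, about 14% of the planned 0.89 SD (9% to 23% for 2 to 5 steered places), rests on an invented number of places, an invented 1 SD advantage, arms of 24 and equal SDs. It shows only that a few selected entries would not be negligible in a trial this small. The case for the change rests on the role description, not on that figure.

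**What to change.** Amend Implementation {16c} as follows.

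- The individual outside the team only generates the list and prepares sealed, sequentially numbered envelopes, and takes no part in enrolment.
- A person without access to the list confirms every eligibility criterion, including ability to adhere, obtains consent and records entry in a log before the next numbered envelope is opened. The principal researcher, who already informs eligible men and seeks consent, could do this.
- Reword Implementation {16c} and the consent section so that they agree on who enrols.

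The cost is a one-paragraph amendment. It needs no added staff and changes neither the sample size nor any clinical procedure. Its reach may be limited: Trial status gives recruitment from 23 October 2023 to about the end of April 2024, so few or no enrolments may remain. Apply it to any that do, and in all cases report who held the list, who made the entry decisions and in what order for the men already enrolled.
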